Obesity is a modifiable risk factor for several cancers, including colorectal cancer [38]. Several studies have evaluated the effects of Mindfulness on eating behavior to support weight management. Stress-induced emotional eating is often associated with the consumption of “comfort foods” that tend to be more energy dense [39]. To determine the effect of Mindfulness on eating behavior, Fulwiler et al. used the “Three-Factor Eating Questionnaire”, an assessment that measures three aspects of eating behavior: cognitive restraint, uncontrolled eating, and emotional eating, to determine if emotional eating shifted in response to a Mindfulness intervention [40]. They presented the hypothesis that high levels of emotional eating could predict weight gain, while low levels of emotional eating could predict weight loss. They found in their study that Mindfulness was associated with reduced levels of emotional eating, but they failed to assess participant weight change [40]. A systematic review and meta-analysis conducted in 2019 evaluated 10 Mindfulness interventions on weight control and found a significant weight reduction among the Mindfulness participants when compared to control groups [41]. Therefore, Mindfulness may reduce emotional eating, energy intake, and weight gain, thus reducing the risk of colorectal cancer.

This paper describes the design of a TRE and Mindfulness intervention among young adults with obesity and CPS. Participants will be randomized to 8 weeks of TRE, Mindfulness, TRE and Mindfulness, or Control. The primary outcomes are related to feasibility and acceptability. Secondary outcomes are related to body weight, body composition, perceived stress, metabolites of the hypothalamic–pituitary–adrenal axis, circulating cardiometabolic disease risk markers, gut microbiome, and colonic inflammation. We hypothesize that the study will be feasible (i.e., recruit ≥ 50% of those approached, retain ≥ 80% of the participants, participants in the intervention groups will complete ≥ 80% of the intervention content, and all groups will complete ≥ 80% of planned assessments) and acceptable (i.e., based on a standardized acceptability survey by Pflugeisen et al. [42], that will be assessed during week 4 of the intervention and after completing the intervention). 

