#### 2.3.4. Randomization

Participants (*n* = 48) will be randomly assigned 1:1:1:1 to the following groups: (1) TRE; (2) Mindfulness; (3) TRE and Mindfulness; or (4) Control. We will use a stratified randomization approach considering sex (female vs. male) to ensure balance across treatment arms. Randomization will occur after all aspects of the baseline data collection are completed.

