#### 2.6.12. Power and Sample Size 

This study is designed to evaluate the feasibility of the development of a larger study. The goal of the trial is to investigate and learn about data management, data collection methodologies, and how to design a larger study in the future. Forty-eight adults will be recruited, allowing for a 20% dropout rate, resulting in completed data collection on 40 individuals, which supports the calculation of confidence intervals for feasibility and effect size components. This feasibility-pilot study is not powered to detect statistically significant effects for improvement in chronic stress and body weight or the secondary/exploratory measures. The minimum detectable difference for these outcomes is 1 standard deviation based on the sample size in each of the four groups (n = 10/arm) between the baseline and post-intervention measurements that are correlated at r = 0.5, alpha = 0.05, and 80% power. We expect that there will be no change between baseline and post-intervention measurements in the control group. We did not consider power for the overall and multiple pairwise comparisons between different groups, nor will we correct for multiple comparisons because of the exploratory nature of the pilot study [67,68,69,70,71]. 

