### 2.7. Data Analytic Plan

Data will be managed using REDCap [72] and analyzed using the statistical software SAS (version 9.4, SAS Institute, Cary, NC, USA). The data will be organized and stored on an encrypted server. Metadata will be available and stored in an electronic lab notebook, including details of what, where, when, why, and how data were collected and processed. 

We will summarize feasibility and acceptability metrics using descriptive statistics such as frequencies, percentages, means, and standard deviations. The results will include the recruitment rate among eligible individuals approached, adherence (i.e., % interaction with asynchronous sessions, % of days adherent to the TRE protocol), % retained through post-intervention, and scores on the acceptability survey. The feasibility and acceptability rates will be estimated as the number of feasibility and acceptability participants divided by the total number of approached participants, respectively. A 95% confidence interval for the feasibility and acceptability rates will be calculated assuming a binomial distribution. Fisher’s exact test will be used to test whether feasibility and acceptability rates are significantly higher than their threshold rates (50% or 80%), respectively. A chi-square test will be used to test its relationship with other categorical clinical factors, and a *t*-test will be used for its relationship with other continuous clinical factors instead. Adjusted logistic regression (binary outcomes) or generalized linear models (GLM) (continuous outcomes) will be employed in multivariate analyses to assess their relationship with each other as clinical factors. 

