Exploratory inferential statistics will be conducted, but no conclusions on the efficacy of the interventions will be drawn from the results. Initially, we will evaluate distributions, identify any outliers, and look for patterns of missing data. The continuous endpoints (stress, body weight, body composition, and cardiometabolic health) will be estimated among each of the groups, and the 95% confidence interval will be constructed assuming normal distribution, respectively. Then, a two-sample *t*-test will be utilized to compare each of the three intervention groups and the control group. GLM will be employed to estimate the adjusted difference in each of the continuous endpoints between the different groups. We will also investigate co-primary (body, weight, objective stress markers) and secondary outcomes (i.e., body composition, PSS, cardiometabolic measures) for between- and within-treatment differences and test for (treatment) × (time) interactions to compare the trends over time using generalized linear mixed models. We will investigate changes in microbial community diversity and composition (ASVs), tryptophan-related metabolites, and systemic and intestinal inflammation changes from baseline to post-intervention by treatment arm. The other binary endpoints will be compared between the different groups using Fisher’s exact test or chi-square test, respectively. Multivariate logistic regression will be further employed to compare these binary endpoints between the different groups, after adjusting for plausible confounders. Odds ratios and 95% confidence intervals will be calculated to evaluate the strength of any association that emerges.

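### With about 12 participants per arm, the planned adjusted logistic regression will often yield no finite odds ratio for some arm contrasts when the binary outcome is common (80% or more) or rare (20% or less)

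*Protocol article*

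**What the plan says.** Section 2.7 mentions logistic regression twice. In the paragraph on feasibility and acceptability, which lists retention among its metrics, it states: "Adjusted logistic regression (binary outcomes) or generalized linear models (GLM) (continuous outcomes) will be employed in multivariate analyses". In the paragraph on exploratory inference, the remaining binary endpoints are first compared between groups by Fisher's exact or chi-square test, and then: "Multivariate logistic regression will be further employed to compare these binary endpoints between the different groups, after adjusting for plausible confounders". Odds ratios with 95% confidence intervals are the promised output. These remaining endpoints are not named, no event rates are given for them, and the confounders are not listed.

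The numbers behind these models are small. Under section 2.3.4 the 48 participants "will be randomly assigned 1:1:1:1 to the following groups", with sex as the stratification factor, so each arm has about 12. Section 2.6.12 states: "Forty-eight adults will be recruited, allowing for a 20% dropout rate, resulting in completed data collection on 40 individuals". The Introduction sets the feasibility targets, among them to "retain ≥ 80% of the participants", with 80% thresholds for intervention content and for assessments as well.

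**The concern.** A logistic model estimates each arm's log-odds relative to a reference arm. If every participant in an arm has the outcome, or none does, maximum likelihood pushes that arm's log-odds to infinity. Any odds ratio involving the arm is then infinite or zero, and its Wald interval is meaningless. This is separation. It is unlikely when outcomes are near 50% and likely when they are very common or very rare in small arms.

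The trial's own targets lie in the second region. With 40 completers of 48 there are only 8 dropouts to support three arm terms plus confounders. Section 2.8.3 anticipates that dropout may differ by group, so retention by arm is a natural question for this pilot. Section 2.6.12 says the sample supports confidence intervals for feasibility and effect-size components, and section 3 says the results will feed a fully powered trial. An output that does not exist for some contrasts does not serve that purpose.

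**Working it through.** **The plan's own figures.** The document gives no figure for the logistic models. Its nearest calculation is the minimum detectable change of 1 SD with 10 per arm, r = 0.5, alpha 0.05 and 80% power. The SD of the change is √(2(1 − 0.5)) = 1 SD. A two-sided paired t-test with n = 10 then has power 0.803, so that figure reproduces. Planned completion is 40/48 = 83.3%, or 8 dropouts; exactly 20% dropout would be 48 × 0.2 = 9.6. Both rates are used below.

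**Chance of an all-or-none arm.** For four independent arms of 12 with the same true rate p:

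- one given arm: q = p^12 + (1 − p)^12
- at least one of four: 1 − (1 − q)^4

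At p = 0.80, q = 0.069 and 1 − 0.931^4 = 0.248.

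| Retention | A given arm, e.g. control, has no dropouts | At least one arm has no dropouts |
|---|---|---|
| 70% | 1% | 5% |
| 80% | 7% | 25% |
| 83.3% | 11% | 38% |
| 85% | 14% | 46% |
| 90% | 28% | 73% |
| 95% | 54% | 96% |

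**Fixed number of dropouts.** With exactly d dropouts spread at random over 48, inclusion–exclusion gives 4·C(36,d)/C(48,d) − 6·C(24,d)/C(48,d) + 4·C(12,d)/C(48,d). For d = 8, C(36,8)/C(48,8) = 0.0802 and C(24,8)/C(48,8) = 0.0019; the last term is negligible. The result is 0.309. The same formula gives 15% for 10 dropouts, 57% for 6 and 89% for 4.

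**Adjusted model.** Separation was tested by linear programming in 1,000 simulated trials per setting, with no true arm effect. Assumptions: about 25% of each arm of one sex, and covariates unrelated to the outcome. The ranges cover a model with arm and sex, and one with two continuous covariates added. Because the problem is symmetric, 80% and 20% behave alike.

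| Outcome rate | 12 per arm | 10 per arm |
|---|---|---|
| 50% | under 0.5% | under 2% |
| 70% or 30% | about 7% | 14–16% |
| 80% or 20% | 28–29% | 44–45% |
| 90% or 10% | 77–80% | 86–87% |

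**What a penalised estimate gives.** Take 12/12 retained against 10/12. The maximum-likelihood odds ratio is infinite. In a model with arm alone, Firth's method equals adding 0.5 to each cell. The odds become 12.5/0.5 = 25 in the first arm and 10.5/2.5 = 4.2 in the second, so the odds ratio is 25/4.2 = 5.95. The variance of the log odds ratio is the sum of the reciprocals of the four cells: 0.08 and 2 for the first arm, 0.095 and 0.4 for the second, in total 2.575. The standard error is √2.575 = 1.60, so the Wald 95% interval is about 0.26 to 138. The estimate is finite, and the interval shows how little 24 people can say.

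**The case against.** The best case for the plan has four parts.

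- **Which endpoints.** The sentence that compares arms by logistic regression covers unnamed endpoints without stated rates. The sentence in the feasibility paragraph relates outcomes to clinical factors and does not expressly announce a four-arm comparison of retention. This stands: the retention figures apply if retention is compared by arm, and for other endpoints the risk depends on their rates.
- **Fisher's exact test is already planned**, as are binomial intervals for the feasibility rates. Both work with a zero cell. But the test is unadjusted and gives no adjusted odds ratio or interval, which is what the plan promises next.
- **The estimator may be settled elsewhere.** The article does not say maximum likelihood, and an analysis plan that is not shown could specify a penalised or exact fit. That is possible. Still, the article commits to a method and an output that fit its own design badly; the point concerns that stated choice, not a missing detail.
- **The analyses are exploratory**, with no efficacy conclusions. This limits the consequence. It excuses low power, but it does not make a non-existent estimate usable.

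A reader might also infer that the surviving odds ratios are biased away from the null. That has not been shown. In simulations with no arm effect, about 20% of finite arm odds ratios lay above 4 or below 1/4. A log-odds-ratio SD of about 1.09 produces this by itself: 2 × (1 − Φ(1.386/1.09)) ≈ 0.20. It is sampling noise, and a null simulation cannot demonstrate bias away from the null.

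**Conclusion.** The point holds in limited form. For binary outcomes at or above 80%, or at or below 20%, with about 12 per arm, ordinary maximum-likelihood logistic regression will often leave at least one arm without a finite odds ratio. For retention compared by arm, the chance is about 25% at 80% retention, 31% with exactly 8 dropouts and 73% at 90%. These figures assume balanced arms, one common true rate and an unpenalised fit; the adjusted figures also rest on the assumed covariates.

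Three broader readings are not supported. First, the whole comparison does not normally fail: only contrasts with the all-or-none arm are lost, and all contrasts with control go only when control is that arm. Second, better retention does not worsen every analysis. It does so when retention or a similar completion measure is the outcome; for endpoints measured in completers, 12 rather than 10 per arm lowers the risk. Third, the pilot does not become unable to inform the larger trial, because the feasibility rates and their binomial intervals are unaffected. The change is worth making because it costs little, not because the trial's main conclusions depend on it.

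**What to change.** In section 2.7, for binary outcomes, do one of the following and keep the planned Fisher's exact test:

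1. Replace the adjusted logistic regression with Firth-penalised logistic regression containing only arm and the stratification factor sex, with profile-likelihood 95% intervals. The plan already uses SAS 9.4, where this is the FIRTH option in PROC LOGISTIC.
2. Replace the adjusted odds ratios with arm-level proportions and risk differences against control, with exact or score 95% intervals.

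Either choice should cover both places where logistic regression is planned. The cost is a change of wording and, for the first option, one software setting. The price is fewer adjustment covariates, slightly shrunken estimates under Firth, and intervals that remain wide.

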### 2.8. Design Considerations

#### 2.8.1. Participant Retention

All participants will receive a monetary subsidy for participating in the trial. They will receive a parking voucher or USD 7 (cash) travel reimbursement for each completed study visit. If they complete the in-person screening and are not eligible to participate in the study, they will receive USD 20 (cash). If they are eligible and complete the baseline visit, they will receive USD 10 (cash) for the in-person screening and USD 60 (cash) for completing the baseline data visit (these are completed in the same visit). Once they complete the post-intervention data collection, they will receive USD 100 (cash). If they complete the study, they will receive a total of USD 170 plus transportation reimbursements. To maximize retention, we will provide financial and logistical support for transportation for the in-person data collection visits. We will also accommodate major holidays (e.g., Thanksgiving Day), allowing for an “off” day. Control participants will be provided with one free dietary weight-loss counseling session and a one-year paid membership to Calm.com after study completion.

#### 2.8.2. Participant Safety 

This trial is classified as a low-risk research study. If participants report any safety concerns, they will be addressed promptly.

#### 2.8.3. Identified A Priori Limitations

As this is a pilot study, several challenges may arise with the execution of the project. First, we may face challenges in finding participants willing to join this study. Mindfulness and TRE interventions are relatively new approaches to stress reduction and weight management that might face difficulties in acceptance. Secondly, we acknowledge the challenge of following a TRE protocol and are aware that we will require the TRE and Mindfulness group to follow the combined protocols, which could require more time commitment from the participants. This might result in differential dropout rates based on the group the participant was assigned to. Third, this study will unlikely demonstrate a significant change in EOCRC development risk, given the nature of the behavioral intervention, the small sample size, and the brief duration of the study. Lastly, the Fitbit data on heart rate variability is not validated by the U.S. Food and Drug Administration, nor are their algorithms made publicly available. However, this type of equipment may be more acceptable in a free-living environment and less biased than measurements derived from a lab environment.

#### 2.8.4. Identified A Priori Innovations

This proposal has several innovations. This will be the first study to assess Mindfulness combined with TRE among any population, including young to middle-aged adults (ages 18–39) at high risk for developing EOCRC. We focus on young adults due to EOCRC being present in adults <50 years old and it currently being on the rise in westernized countries, and we would like to focus on EOCRC prevention. This study is among the first to assess CPS both objectively [through measurement of HCORT, adrenocorticotropic hormone, epinephrine, and norepinephrine via blood] and subjectively (through application of the PSS) in the context of a combined TRE and Mindfulness intervention. HCORT is a robust measure of hypothalamic–pituitary–adrenal axis function and recent past or ongoing stress that is responsive to short-term Mindfulness interventions (<8 weeks) [73]. We will implement a remote digital Mindfulness and TRE intervention in an asynchronous format. This approach holds potential for low-cost integration into healthcare systems and for wide dissemination. Lastly, this study will attempt to explore TRE and Mindfulness’s effect on behavioral, anthropometric, hormonal, metabolic, immune, and gut microbial endpoints that link CPS to EOCRC.

## 3. Discussion and Conclusions

EOCRC is increasing in the US and other Westernized nations. Obesity and CPS are considered modifiable risk factors for the EOCRC. Our trial will be among the first to combine TRE and Mindfulness in an effort to mitigate stress and promote weight loss among young to middle-aged adults at risk of EOCRC. The feasibility and preliminary data generated here will assist in developing a fully powered efficacy trial testing the efficacy of TRE and Mindfulness for EOCRC prevention.

This study contributes to the field by assessing the combined effects of TRE and Mindfulness in a high-risk population for EOCRC. It also incorporates objective and subjective measures of CPS, explores the potential of remote digital interventions, and investigates various endpoints linking CPS to EOCRC. Findings from this study will inform the development of larger studies and provide valuable insights into stress reduction and weight management strategies for EOCRC prevention.

## Figures and Tables

**Figure 1 nutrients-16-00504-f001:**
[figure not shown]
Study design. TRE = Time-restricted eating, ad libitum food intake from 12 a.m.–8 p.m.; Mindfulness: mindfulness-based stress reduction asynchronous intervention; Control = ad libitum food intake and no Mindfulness intervention (created with BioRender.com).

**Table 1 nutrients-16-00504-t001:** Inclusion and exclusion criteria.

**Inclusion Criteria**
(1) 18–39 years old.
(2) BMI: 30–49.99 kg/m^2^.
(3) Own and use a smartphone, computer, or tablet with access to the Internet.
(4) Score ≥ 14 on the Perceived Stress Score (PSS) at screening.
**Exclusion Criteria**
(1) Have a personal or family history of EOCRC.
(2) Have taken antibiotics in the previous 2 months.
(3) Have an inflammatory bowel disease or genetic predisposition to EOCRC or CRC (e.g., Lynch syndrome).
(4) Any cancer diagnosis or cancer treatment in the past 12 months.
(5) Consume >50 g of ethanol daily (approximately 4–5, 12 ounce beers).
(6) Use combustible tobacco.
(7) Have a history of bariatric surgery or bowel resection.
(8) Have an active infection.
(9) Have type 1 or type 2 diabetes, immunodeficiency/autoimmune disorder, or inflammatory bowel disease.
(10) Use fiber or pre-/probiotic supplements ≥3 days per week.
(11) Currently taking corticosteroids medication—inhaled, topical, or oral—in the past 2 months (affects cortisol measures).
(12) Are on a weight-loss diet or involved in a formal weight-loss program or are not weight stable for 3 months (+/−4.5 kg) prior to the study.
(13) Females who are pregnant or are trying to become pregnant.
(14) Have schizophrenia (medication can affect study outcomes).
(15) Have an eating window of <10 h/day or are currently following an intermittent fasting pattern.
(16) Night shift workers (shift passes midnight).
(17) Present a history of eating disorders.
(18) Currently taking weight-loss medication.
(19) Illegal drug use in the past month (not marijuana).

**Table 2 nutrients-16-00504-t002:** The weekly provided Mindfulness content.

Week 1	Week 2	Week 3	Week 4	Week 5	Week 6	Week 7	Week 8
1: The Big Idea (10 min)	5: A Habit You Actually Want (10 min)	9: Into the Still point (11 min)	13: Body Wisdom (14 min)	17: The Waxy Build-up (13 min)	21: The Happiness Hit (11 min)	25: Meditation Muscle Groups (13 min)	29: Cosmic Burpee (11 min)
2: Homebase (9 min)	6: The Concentration Gym (11 min)	10: Eye of the Hurricane (10 min)	14: A Space Odyssey (13 min)	18: Welcome to the Party (10 min)	22: Strong Compassion (11 min)	26: The Do-Nothing Project (10 min)	30: Take the Power Back (13 min)
3: Pop out of your thoughts (10 min)	7: The Sweet Spot (10 min)	11: Electric Clarity (11 min)	15: Roller Coaster (13 min)	19: Slow Motion (10 min)	23: (Self) Love Bomb (13 min)	27: No Agenda (10 min)	-
4: Inner Smoothness (11 min)	8: Even Flow (10 min)	12: Sanity Day (14 min)	16: Free and Clear (14 min)	20: Better at Everything (11 min)	24: Connected from the Inside (11 min)	28: The Answer (10 min)	-

